### Study Participants

#### Inclusion and Exclusion Criteria

Study eligibility criteria are parents and caregivers who are pregnant or have a child 0-18 years old living with them who reside in Allegheny County, PA. Multiple children per family may enroll in the study between ages 0-18 years old. Children and youth will participate in completing surveys themselves starting at age 8 years old. Currently, the study is open to participants who speak English and Spanish.

#### Recruitment Strategy

Families enrolled in all TPS cohorts are invited to participate in the TPS THRIVE Study. Each of the TPS age cohorts have tailored recruitment strategies based on sample size, intervention site, and intervention delivery. Collaboratives partnered with multiple organizations to recruit pregnant women, new mothers at maternity hospital sites, Special Supplemental Nutrition Program for Women, Infants, and Children (WIC) offices, Federally Qualified Health Centers (FQHCs), and pediatric primary care offices throughout the region. School-based studies recruit families of students enrolled in participating schools and community organizations.

#### Participant Retention

TPS developed partnerships with key leaders in different communities across Allegheny County to serve as TPS Community Ambassadors to enhance connections with communities involved in the study. TPS Community Ambassadors and other community-partner organizations support community outreach and participant recruitment and retention. All participants (children, youth, and caregivers) receive incentives for completing each survey. In addition, TPS offers multiple methods of data collection (in-person, online, by phone) to increase response rates and implement retention best practices for follow-up, reminders, and outreach.

#### Participant Withdrawal

Participants can withdraw from the study for any reason at any time. Changes in child custody, parent/caregiver status, or residence may make the participant ineligible to continue in the study. Study staff will record the reasons for withdrawal and non-retention.

#### Sample Size

Our sampling frame will combine the current TPS study participants across cohorts. For early childhood (0-5 years old), the planned sample size is 7,500. With an estimated response rate of 50% for the first annual THRIVE assessment (3,750 participants), and an 85% retention rate for the second annual assessment, we will have a final sample size of 3,187 children 0-5 years old over 2 years. This will provide the ability to detect a 0.08 difference in parent thriving Brief Inventory of Thriving (BIT) score and 5.5% difference in prevalence of child flourishing with a power of 85% (alpha = 0.05).

For school-age children and adolescents, the planned sample size is 4,930. With an estimated response rate of 50% for the first annual assessment (2,465 participants), and an 85% retention rate for the second annual assessment, we will have a final sample size of 2,095 children and youth 6-18 years old over 2 years. For our sample of 6- to 18-year-old children, our study will have the power to detect a 1-point difference in our main outcome of youth thriving (85% power, alpha of 0.05; BIT mean score (SD): 3.71 (0.78)).

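### The power statement for ages 6-18 is internally inconsistent: its own N, SD, power and alpha give a detectable difference of about 0.10 BIT point for two equal groups, not 1 point

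*Protocol article*

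**What the plan says.** The Sample Size section of the protocol article builds the 6-18 sample in three steps. It starts from the planned number ("For school-age children and adolescents, the planned sample size is 4,930"), applies the first-year response ("With an estimated response rate of 50% for the first annual assessment (2,465 participants") and then year-two retention ("an 85% retention rate for the second annual assessment"). The result is stated as "we will have a final sample size of 2,095 children and youth 6-18 years old over 2 years".

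The power claim follows; the study is said to have "power to detect a 1-point difference in our main outcome of youth thriving (85% power, alpha of 0.05; BIT mean score (SD): 3.71 (0.78"). Under Primary Outcome Measures, the score on the 10-item Brief Inventory of Thriving (BIT) is the primary outcome for this age group, so this is the power statement for a primary outcome.

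The paragraph just before it covers ages 0-5, with a final sample of 3,187 at the same power and alpha: "This will provide the ability to detect a 0.08 difference in parent thriving Brief Inventory of Thriving (BIT) score and 5.5% difference". No SD is given for that parent score.

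Neither paragraph says which groups or time points are compared, whether the test is one- or two-sided, or how the sample divides.

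**The concern.** A difference of 1 point against an SD of 0.78 is 1/0.78 = 1.28 SD. A sample of more than 2,000 children should detect something far smaller at 85% power. The neighbouring paragraph says so for the same instrument: 0.08 point with about one and a half times as many children (3,187/2,095 = 1.52). The two stated differences are 12.5-fold apart (1/0.08), whereas the sample sizes alone would account for a factor of √1.52 = 1.23.

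What is at stake is how the study's sensitivity is understood. A reader who takes the sentence at face value would conclude that the 6-18 component can reliably see only very large differences. That reader would judge the planned subgroup and longitudinal comparisons against a benchmark that is too coarse by about an order of magnitude.

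**Working it through.** **Inputs** (Sample Size section): planned 4,930; response 50%; retention 85%; final N 2,095; SD 0.78; power 85%; alpha 0.05. Two-sided testing is assumed, because sidedness is not stated. Normal quantiles: 1.960 + 1.036 = 2.996.

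**1. Sample size chain.** 4,930 × 0.50 = 2,465, and 2,465 × 0.85 = 2,095.25. The stated 2,095 reproduces.

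**2. Detectable difference, two equal independent groups.** Difference = (z for alpha + z for power) × SD × 2/√N = 2.996 × 0.78 × 2/√2095 = **0.102** point, or 0.102/0.78 = 0.13 SD. One-sided testing gives 0.091. The stated 1 point does not reproduce.

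**3. Power at the stated and recomputed differences.** The standard error is 0.78 × 2/√2095 = 0.0341.
- At 1 point the expected z is 1/0.0341, about 29, so power is essentially 100%.
- At 0.10 point the expected z is 2.93, so power is 83.5%.
- For 1 point at 85% power, n per group = 2 × (2.996 × 0.78)² = 10.9, so 11 children per group (about 12 with a t correction).

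**4. Other readings of the comparison.** The text does not fix it, so it was varied with N = 2,095 and a two-sided test unless noted.

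| Reading | Detectable difference (points) |
|---|---|
| Paired, within-subject correlation 0 to 0.7 (assumed): 2.996 × 0.78 × √(2(1−r))/√2095 | 0.072 down to 0.040 |
| One-sample, SD 0.78 | 0.051 |
| Two equal groups at baseline, N = 2,465 | 0.094 |
| Unequal groups, 20% / 13% / 5% / 2% in the smaller (illustrative): 2.996 × 0.78/√(N q(1−q)) | 0.128 / 0.152 / 0.234 / 0.365 |
| Two equal groups, design effect 1.5 to 5 (illustrative) | 0.13 to 0.23 |

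None comes near 1 point.

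**5. What 1 point would require.** With two equal groups, one of these would be needed:
- a design effect of (1/0.1021)², about 96; or
- an SD of √2095/(2 × 2.996), about 7.6, against the printed 0.78.

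With unequal groups, the smaller one would have to hold only 5 or 6 of the 2,095 children.

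**6. Comparison with the 0-5 figure.** The same two-equal-group formula with N = 3,187, and SD 0.78 assumed for parents, gives 2.996 × 0.78 × 2/√3187 = 0.083, against the stated 0.08. Scaling in the other direction, 0.08 × √(3187/2095) = 0.099.

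**7. Sum-score reading.** The BIT has 10 items. If the score were a sum, the SD would be 10 × 0.78 = 7.8 and the detectable difference 10 × 0.102 = 1.02 points. On that scale the mean would be 37.1, not the printed 3.71.

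**The case against.** Four points can fairly be made for the plan.

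- **The replacement value is not fixed by the text.** No comparison, allocation or sidedness is named. Study Comparison Groups speaks of paired tests for change, and Data Analysis of random-intercept models. This stands: 0.10 depends on assuming two equal independent groups and a two-sided test, and a paired reading gives less. But no reading tried restores 1 point.

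- **The fault may be one of units.** One point could be right on the 10-item sum scale (1.02). That is possible, though the document does not say so. The sentence would then pair a sum-scale difference with an item-mean mean and SD, and would still need correction. It does mean that there are two valid repairs.

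- **The 0.08 comparator is only suggestive.** It concerns parents in the 0-5 cohort and comes without an SD. This stands: it supports the two-equal-group reading if the SDs are similar, and proves nothing by itself.

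- **The sentence is conservative.** The study does have at least 85% power for 1 point, so the statement is true in a loose sense. But 1 point is not the difference at which power is 85%, which is how the parenthesis presents it.

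A reader might also infer that the 6-18 sample is too small, or that a null result could not be interpreted. The document supports neither. N comes from existing cohort participants multiplied by response and retention rates, not from the 1-point figure. No decision rule uses that figure, and a null result would be read from its confidence interval, whose width does not depend on this sentence.

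**Conclusion.** The point holds as an internal inconsistency in a stated power figure for a primary outcome: a 1-point detectable difference, SD 0.78, N = 2,095, 85% power and alpha 0.05 cannot all be right. For two equal independent groups and a two-sided test the stated difference is about ten times too large. Under a paired or one-sample comparison the gap is wider, and under the unequal splits and design effects tried it is narrower but still substantial (0.365 at most).

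The likely origin is a slip for 0.1 or a mix of item-mean and sum scales; the document does not show which. Reading 3.71 and 0.78 as item means is itself an inference. It rests on the 10-item format and on items being scored from 1 upward, which the article does not state.

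The direction of the error is to understate sensitivity. The sample size, the analyses and participants are unaffected.

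**What to change.** Rewrite the one sentence in either of two ways:

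- keep mean 3.71 and SD 0.78, and state a detectable difference of about 0.10 point (0.13 SD); or
- put the difference, mean and SD all on the 10-item sum scale.

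In both cases say which scoring of the BIT is used, which comparison the figure refers to (two independent groups with their allocation, or change within child with the assumed correlation), and whether the test is two-sided. If a within-child comparison was intended, replace 0.10 with the matching value, about 0.04 to 0.07 for correlations of 0.7 down to 0. Any values shown for unequal groups should be labelled illustrative, since the article gives no allocation for this claim.

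The cost is one corrected sentence. Nothing changes in recruitment, design or analysis.

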### Study Comparison Groups

TPS combines family, school, and neighborhood-level interventions, targeting contexts most relevant to improving child outcomes by developmental age. For baseline survey data, descriptive analyses will assess mean levels of outcomes across subgroups (by age, sex, race/ethnicity, and family income). We will examine changes over time using paired *t*-tests and adjusted linear regression models for continuous outcomes and McNemar tests and adjusted logistic regression models for categorical variables.

### Study Outcomes and Measures

Table 2 provides an overview of the outcomes and assessments mapped to the conceptual framework domains of thriving.

**Table 2 T2:** Cross-cutting study measures, assessments, and ages.

**Domain**	**Measure/data source**	**Respondent**	**Ages**
**Strong bodies**			
Overall health	PROMIS global health (29)	Caregiver, youth	0–18
Physical activity	PROMIS physical activity (30) Outdoor time	Caregiver, youth	0–18
Eating/nutrition	YRBS (31)	Caregiver, youth	0–18
Height and weight	Self-report, HER	Caregiver, youth	0–18
Sleep	PROMIS sleep health—disturbance and impairment (32)	Caregiver, youth	0-18
Screen time	NSCH screen time (33)	Caregiver, youth	0–18
Health behaviors	YRBS (31)	Youth	12–18
Alcohol, tobacco, and drug use	YRBS (31)	Youth	8–18
Sexual activity	YRBS (31)	Youth	12–18
**Strong minds**			
Child mental health	NSCH mental health diagnoses (33) PROMIS anxiety and depression (34)	Caregiver, youth	0–18
School readiness	NSCH healthy and ready to learn (33)	Caregiver	3–5
School connectedness	YRBS (31)	Caregiver, youth	6–18
Parent engagement	YRBS (31)	Caregiver	6–18
School attendance	YRBS (31)	Caregiver, youth	6–18
Academic performance	YRBS (31), school records	Caregiver, youth	6–18
**Positive identity and self-worth**			
Learning behaviors	PROMIS curiosity, persistence, and adaptation	Caregiver	0–5
Thriving, future orientation/hope	NSCH Flourishing Index (33) Brief Inventory of Thriving (35)	Caregiver, youth	6–18
Meaning and purpose	PROMIS meaning and purpose (36)	Caregiver, youth	6–18
Resilience	Youth Thriving Survey resilience subscale (37)	Caregiver, youth	6–18
**Fun and happiness**			
Child positive affect	PROMIS positive affect (38)	Caregiver, youth	0–18
**Caring family and relationships**			
Family relationships	PROMIS family relationships (39)	Caregiver, youth	0–18
Family routines	CDC National Survey of Early Childhood - Family routines (40)	Caregiver, youth	0–18
Family resilience	NSCH family resilience (33)	Caregiver, youth	0–18
Peer relationships	PROMIS peer relationships (41)	Caregiver, youth	0–18
Caregiver social support	PROMIS instrumental, emotional, and informational support (42)	Caregiver	0–18
Caregiver stress	Parental perceived stress (43)	Caregiver	0–18
Caregiver thriving	Human Flourishing Scale (44)	Caregiver	0–18
Caregiver relationships	Dyadic Adjustment Scale (45)	Caregiver	0–18
**Safety**			
Neighborhood safety	Perceived Neighborhood Safety Scale (46)	Caregiver, youth	0–18
Exposure to violence and bullying	YRBS (31)	Caregiver, youth	8–18
**Vibrant communities**			
Neighborhood satisfaction	Neighborhood Satisfaction Scale (47)	Caregiver, youth	0–18
Collective efficacy	Collective efficacy (48)		
Access to green space	PHENOTYPE items (49)	Caregiver, youth	0–18
Transportation	Protocol for Responding to and Addressing Patient's Assets, Risks, and Experiences (PRAPARE) (50)	Caregiver	0–18
Safety	PRAPARE relationships (50)		
**Healthy environments**			
Housing quality	American Housing Survey (47)	Caregiver	0–18
Water safety	American Housing Survey (47)	Caregiver	0–18
Lead exposure	Blood lead levels	Caregiver, EHR	0–18
Air quality Exposure to smoke	Secondary data NSCH Exposure to Smoke (33)	Caregiver	0–18
Food security	USDA Food Security Screener (51)	Caregiver	0–18
**Racial justice, equity, inclusion**			
Racism and discrimination	Multigroup Ethnic Identity Measure (52), Perceived Discrimination Scale (53)	Caregiver, youth	0–18
Socialization	Cultural Socialization Behaviors Measure (54)	Caregiver	0–18
Religion/spirituality	Spiritual well-being (55)	Caregiver, youth	0–18
**Healthcare services**			
Usual source of care and service use	NSCH usual source of care and health service use (33)	Caregiver	0–18
Health insurance and costs	NSCH health insurance (33)	Caregiver	0–18
Trust in medical providers	Abbreviated Trust in Physicians Scale (56)	Caregiver	0–18
Immunizations	Parent Attitudes about Childhood Vaccines Survey (57)	Caregiver	0–18
Primary Care Communication	Parents perceptions of pediatric primary care quality (58), Interpersonal Processes of Care Survey (59)	Caregiver report	0–18
Health information	Consumer Health Information (60)	Caregiver report	0–18
Health literacy	Abbreviated Health Literacy Measure (61)	Caregiver report	0–18

*Family demographic data will also be collected including child and caregiver age, race/ethnicity, primary language, and gender identity; primary and secondary caregiver income, employment, education, use of other social services; residential history; Household size, number of children*.

#### Primary Outcome Measures

Primary outcomes of TPS THRIVE are child/youth thriving measures across developmental stages. The early childhood (ages 0-5 years old) primary outcome is the National Survey of Children's Health (NSCH) (3) measure of thriving/flourishing. For school-age children and youth (aged 6-18 years old), the primary outcome is thriving score on the Brief Inventory of Thriving (BIT), a 10-item assessment of youth psychological well-being (35).

#### Secondary Outcome Measures

Secondary outcome measures for early childhood (0-5 years) are the National Institutes of Health (NIH) Patient Reported Outcome Measure Information System (PROMIS) (2) measures of thriving/flourishing, including curiosity, persistence, adaptability, supportive relationships, and positive affect, as well as the NSCH Healthy and Ready to Learn measure of school readiness (62). For school-age and adolescent children, secondary outcomes are future orientation, PROMIS measures of meaning and purpose (36), and academic proficiency (reading and math scores) and achievement (grade completion and graduation).

#### Social Influences on Health Measures

Intermediate outcomes include social influences on health including cross-cutting study measures and assessments of family, school, and community factors that influence child and youth thriving outcomes including:

Influence of policy and place on child thriving, such as neighborhood-level collective efficacy (48), experiences of racism/discrimination (52, 53), access to community resources, and neighborhood safety (46).Influence of physical and social environments on child thriving, including water/air/housing quality, child/school experiences, and positive and adverse child experiences (47).Influence of health services delivery on child thriving, including access to health care, trust in health care providers (56), and health literacy (61) and communication (59).

### Study Procedures and Data Collection

#### Primary Data Collection

The TPS THRIVE study is administered online, with options for phone and in-person completion for participants who may not have access to technology or have other barriers to online completion. Planned future assessments include physical assessments, biomarkers, genetic information, and environmental samples. Study questionnaires and data collection forms can be found on the Study SharePoint site.

#### Secondary Data Collection

The study also combines parent/caregiver and youth (ages 8-18 years) reported survey data with administrative and secondary data, including child and caregiver electronic health records (EHRs), birth certificates, and geospatial community data. Enrolled participants are asked for permission to access health service encounters and assessments from medical records, health and social service use from health and human service departments, school record data, and other administrative secondary data. This Healthy Environment, Strong Bodies Committee synthesizes local data sources, research studies, and collaborative initiatives focused on selected exposures of high interest to the community: psychosocial stress, air quality, water quality, chemical contaminants, infectious disease, green space, and food security.

#### Training and Certification

Study personnel will be trained within each intervention study and centrally in the study protocol requirements, including standardized measurement and eliciting information from study participants in a uniform reproducible manner. The TPS Study Coordinator and Cohort Coordinators will review how to collect data and conduct the procedures at each visit in detail. All study staff including community members will complete required training in human subjects research ethics, data privacy, and data security procedures.

### Data Management

#### Data Entry and Tracking

The Center for Research on Health Care Data Center (CRHC-DC) serves as the Data Core for TPS. The Data Core develops strategies for study data entry and management. Data are entered electronically via a password-protected web-based data entry system, but paper versions of forms are provided for manual entry in case of technical problems. Our web-based system, developed using ASP.NET programming, adheres to guidelines set by FDA 21 CFR Part 11, which mandates practices with respect to data access, data confidentiality, password protection, audit trails, validation, and direct data entry. The data entry process begins during the online participant registration into TPS which generates a participant ID at initiation to track participants, link data, and maintain data confidentiality. The tracking system produces a schedule of data collection for each participant. TPS study coordinators log into the data entry and tracking system, enter the participant's study ID, and choose the visit to be viewed. The appropriate set of forms are generated for that participant based on the visit number. To minimize missing data, all study forms have certain key fields that are required before forms can be submitted. The web-based system can link each TPS study participant across multiple cohorts and across multiple family members.

#### Data Monitoring

The TPS web-based data management system will track the progress of participants throughout individual studies. The tracking and reporting systems are integrated within the web-based data management system. They include programmed follow-up intervals to allow TPS study personnel to determine which participants are due for a particular visit. The customized tracking system allows TPS to generate reports for monitoring of study progress on recruitment, visit completion, retention, and safety. The TPS Equity, Ethics, and Community Accountability committee will review reports of any adverse events and potential harms to study participants and participating communities and populations.

#### Data Protection and Access

Personal information about potential and enrolled participants are collected and maintained to protect confidentiality before, during, and after the study. Online data access is restricted to authorized study personnel through the password protected data system. Any hard-copy study-related information will be stored securely at the study site, and all participant information will be stored in locked file cabinets in areas with limited access. All reports, data collection, process, and administrative forms will be deidentified using a coded identifier to maintain participant confidentiality. All records that contain names or other personal identifiers, such as locator forms and informed consent forms, will be stored separately from study records identified by code number. Contact forms and any other listings that link participant ID numbers to other identifying information will be stored in a separate folder with limited access. The data team will have access to the final study dataset. Limited data sharing agreements have been developed to link participant data with secondary data with participant permission.

#### Data Quality

During data entry, several strategies are employed to ensure quality of data: use of standard methods of data collection and recording, careful programming of the data management system, detailed documentation of computer operations and data editing procedures, and regular meetings with project staff to review any changes in procedure. TPS Data Core verifies all data, programs out-of-range data checks into data entry fields, and evaluates the full data process within and across forms. TPS Data Core personnel check outlying values from enrollment of the first participant to the data-cleaning phase, conducting logical checks and analyzing outliers. Audit logs will track changes to information previously submitted and recorded on electronic forms to ensure data integrity. Information about the person responsible for the change, the date of the change, the previous entry in the data field, the new entry in the data field, and the reason for the change are recorded and displayed in the electronic forms audit trail.

